**In the Past 7 days:**

1. I have been able to laugh and see the funny side of things
 As much as I always could
 Not quite so much now
 Definitely not so much now
 Not at all

2. I have looked forward with enjoyment
 As much as I ever did
 Rather less than I used to
 Definitely less that I used to
 Hardly at all

3. I have blamed myself unnecessarily when things went wrong
 Yes, most of the time
 Yes, some of the time
 Not very often
 No, never

4. I have been anxious or worried for no good reason
 No, not at all
 Hardly ever
 Yes, sometimes
 Yes, very often

5. I have felt scared or panicky for no very good reason
 Yes, quite a lot
 Yes, sometimes
 No, not much
 No, not at all

6. Things have been getting on top of me
 Yes, most of the time I haven’t been able to cope at all
 Yes, sometimes I haven’t been coping as well as usual
 No, most of the time I have coped quite well
 No, I have been coping as well as ever

7. I have been so unhappy that I have had difficulty sleeping
 Yes, most of the time
 Yes, sometimes
 Not very often
 No, not at all

8. I have felt sad or miserable
 Yes, most of the time
 Yes, quite often
 Not very often
 No, not at all

9. I have been so unhappy that I have been crying
 Yes, most of the time
 Yes, quite often
 Only occasionally
 No, never

10. The thought of harming myself has occurred to me
 Yes, quite often
 Sometimes
 Hardly ever
 Never

Appendix D. FUll Screen InteRview
 *BEFORE WE BEGIN OUR INTERVIEW, I HAVE TO INFORM YOU THAT ALTHOUGH THE INTERVIEW WILL BE CONFIDENTIAL, THERE ARE CERTAIN LIMITS TO CONFIDENTIALITY INCLUDING: IF YOU POSE AN IMMEDIATE THREAT TO YOUR LIFE, OR ANOTHER INDIVIDUAL’S LIFE, AND IF YOU DISCLOSE INFORMATION SUGGESTING THAT ANY CHILD IS AT RISK OF ABUSE, CONFIDENTIALITY WILL BE BROKEN.**Client UNDERSTANDS LIMITS of confidentiality*

| ***Demographic Data*** | |
| --- | --- |
| Client Name: | Date of Birth (DD/MM/YYYY) |
| Address: | Appt #: |
| City: | Postal Code: |
| Phone No.: (home)  (work)  (other)  Phone No. during the day: | Can we contact you by: (Y or N)  Phone _______ Letter______  Leave Message____ Email_____ |
| Health Card No.: |  |
| Date of Screening: |  |

*Are you currently on any medication for any of the problems that I asked you about today?*

Yes (List medications) ______________________________________________

___________________________________________________________________

___________________________________________________________________

No

If ‘YES’: *For how long have you been taking the medication?* _____________________

______________________________________________________________________
*When did you last have a change in the dosage?_______________________________*

______________________________________________________________________
(If less than 1 month: inform the person that we will need to wait until the medication has been stabilized for 1 month)

*Will you inform us if your medication changes or if you begin a new medication?*

Yes  No

*Are you currently in (psychological) treatment for any of the problems that I asked about today?*  Yes  No

*Will you tell us if you begin treatment for any of the problems that I asked you about today?*  Yes  No

*Have you previously been in treatment for any of the problems that I asked about today?*  Yes  No

If ‘Yes’, *when?* _____________________________________________________________________

*What kind of therapy was it?* ______________________________________________________________________

Do you have involvement with other agencies: (Addiction Services, Crisis Services, RCMP, Social Services)

_____________________________________________________________________

*Do you have any illnesses or medical conditions?* (List below) ____________________

_______________________________________________________________________

*Is there a possibility that this/these could interfere with your ability to participate in this* ***Online Therapy USER*** *program?*  Yes  No

*In order to provide some background information to your therapist, can I ask you a few personal questions?*

**Personal History:**

Ethnicity:

Marital Status:

Spousal or partner problems:

Will your partner know that you are participating?  Yes  No

How many children do you have? What are their ages?

Do you use childcare services (e.g., daycare, preschool)?  Yes  No

If yes, please explain:­­­­­­____________________________________________________________________

Please answer the following questions regarding your *most recent child*:

Vaginal Delivery: Yes  No

Breastfeed: Yes  No

Twin Births: Yes  No

Complications with delivery: Yes  No

If yes, please explain_________________________________________________________

Any health concerns with the infant? Yes  No

If yes, please explain_________________________________________________________

**Additional Demographic Questions:**

Family Psychiatric/Medical History (e.g. Depression, Addictions etc.)___________________________________________________________________________

Abuse Within/Outside the Family (e.g. Sexual, Physical, Verbal, Emotional)______________________________________________________________________________
Who do you turn to for support? ___________________________________________________

Are you currently working outside of the home or are you on maternity leave?

Employer? ____________________________________

How long have you done this? _________________________________months / years

Total length of maternity leave?

Living Arrangement:  Alone  With Family  With Friends
 Other: _____________________________________________________________________________

Are you facing any current legal difficulties right now?:

**Medical History:**

Prescription Drugs:

Non-Prescription Drugs:

Addictions:

Tobacco Use:

Alcohol Use:

Illicit Drugs:

Gambling:

Treatment:

*Thanks for answering these questions.*

*Do you have any questions for me?*

APPENDIX E. THE MINI-INTERNATIONAL NEUROPSYCHIATRIC INTERVIEW (MINI)^[[2]](#footnote-2)^

**A. MAJOR DEPRESSIVE EPISODE (MINI PLUS)**

**(**→**means: go to the diagnostic boxes, circle NO in all diagnostic boxes, and move to the next module)**

A1 a Have you **ever** been consistently depressed or down, most of the day, NO YES

nearly every day, for at least two weeks?

If **A1a** = **yes**:

b Have you been consistently depressed or down, most of the day, nearly every day, NO YES

for the past 2 weeks?

A2 a Have you **ever** been much less interested in most things or much less able to enjoy NO YES

the things you used to enjoy most of the time over at least 2 weeks?

If **A2a** = **yes**:

b In the past 2 weeks, have you been much less interested in most things or much NO YES

less able to enjoy the things you used to enjoy most of the time.

→****

is **A1a** or **A2a** coded **YES?** NO YES

**if currently depressed** (**A1b** or **A2b** = **YES**), **explore the current episode AND the most symptomatic past episode.** otherwise explore the most symptomatic past episode.

A3 **Over the two week period when you felt depressed or uninterested,**

Current Episode Past Episode

a Was your appetite decreased or increased nearly every day? Did NO YES NO YES

your weight decrease or increase without trying intentionally

**(**i.e., by ±5% of body weight or ±8 lbs. or ±3.5 kgs. for a

160 lb./70 kgs.person in a month)? If **YES** to either, code **YES**.

b Did you have trouble sleeping nearly every night NO YES NO YES

(difficulty falling asleep, waking up in the middle of the night,

early morning wakening or sleeping excessively)?

c Did you talk or move more slowly than normal or were you fidgety, NO YES NO YES

restless or having trouble sitting still almost every day?

d Did you feel tired or without energy almost every day? NO YES NO YES

e Did you feel worthless or guilty almost every day? NO YES NO YES

IF **A3e** = **YES**: ask for an example*.*The example is consistent with a delusional idea. No Yes

f Did you have difficulty concentrating or making decisions NO YES NO YES
almost every day?

g Did you repeatedly consider hurting yourself, feel suicidal, NO YES NO YES

or wish that you were dead?

→****

A4 Are **3** or more  **A3** answers coded **YES** (or **4 A3** answers, NO YES NO YES

if **A1a** or **A2a** are coded **NO** for past episode or if **A1b** or **A2b** are coded **NO** for current episode)?

**Verify if the positive symptoms occurred during the same 2 week time frame.**

If **A4** is coded **NO** for current episode then explore **A3a** - **A3g** for most symptomatic past episode.

→****

A5 Did the symptoms of depression cause you significant distress or impair NO YES

your ability to function at work, socially, or in some other important way?

A6 Are the symptoms due entirely to the loss of a loved one (bereavement)

and are they similar in severity, level of impairment, and duration to

what most others would suffer under similar circumstances?

If so, this is uncomplicated bereavement.

→****

has uncomplicated bereavement been ruled out? NO YES

A7 a Were you taking any drugs or medicines just before these symptoms began?

No Yes

b Did you have any medical illness just before these symptoms began?

No  Yes

in the clinician’s judgment: are either of these likely to be direct causes of the patient's depression?
If necessary ask additional open-ended questions.

**A7 (summary**):has an organic cause been ruled out? NO YES UNCERTAIN

| A8code **yes** if **A7(summary)** = **yes** or **uncertain**.  Specify if the episode is current AND/ or past OR BOTH (recurrent). | **NO YES**  ***Major Depressive Episode***  Current  Past |
| --- | --- |

| A9code **yes** if **A7b** = **yes** and**A7 (summary)** = **no**.  Specify if the episode is current AND/ or past OR BOTH (recurrent). | **NO YES**  ***Mood Disorder Due to a***  ***General Medical Condition***  Current  Past |
| --- | --- |

| A10code **yes** if **A7a** = **yes** and **A7 (summary)** = **no**.  Specify if the episode is current AND/ or past OR BOTH (recurrent). | **NO YES**  ***Substance Induced Mood Disorder***  Current  Past |
| --- | --- |

CHRONOLOGY

| A11 | How old were you when you first began having symptoms of depression? |  | age |  |  |  |  |
| --- | --- | --- | --- | --- | --- | --- | --- |

| A12 | During your lifetime, how many distinct times did you have these symptoms |  |  |  |  |  |  |
| --- | --- | --- | --- | --- | --- | --- | --- |

of depression (daily for at least 2 weeks)?

| A13 | Is there any family history of bipolar disorder or any relative ever treated with a  mood stabilizer? | Yes |  | No |  |  |  |
| --- | --- | --- | --- | --- | --- | --- | --- |

**SUBTYPES OF MAJOR DEPRESSIVE EPISODE Mark all that apply.**

Mild  296.21/296.31

Moderate  296.22/296.32

Severe without psychotic features  296.23

Severe with psychotic features  296.24

In partial remission  296.25

In full remission  296.26

Chronic

With catatonic features

With melancholic features

With atypical features

With postpartum onset

With seasonal pattern

With full interepisode recovery

Without full interepisode recovery

**B. SUICIDALITY (MINI)**

Points

**In the past month did you:**

B1 Suffer any accident? This includes taking too much of your medication accidentally. NO YES 0

IF NO TO B1, SKIP TO B2; IF YES, ASK B1a:

**B**1a Plan or intend to hurt yourself in any accident either actively or passively (e.g. by not avoiding a risk)? NO YES 0

IF NO TO B1a, SKIP TO B2: IF YES, ASK B1b:

B1b Intend to die as a result of any accident? NO YES 0

B2 Feel hopeless? NO YES 1

B3 Think that you would be better off dead or wish you were dead? NO YES 1

B4 Think about hurting or injuring yourself or have mental images of harming yourself, NO YES 4 with at least some intent or awareness that you might die as a result?

How many times? _____

B5 Think about suicide (killing yourself)? NO YES 6

How many times? _____

IF NO TO B5, SKIP TO B7. OTHERWISE ASK:

Frequency Intensity

Occasionally πMild π

Often πModerate π

Very often πSevere π

B6 Feel unable to control these impulses? NO YES 8

| B7 | Have a suicide method or plan in mind (e.g. how, when or where)? | NO | YES | 8 |
| --- | --- | --- | --- | --- |

IF NO TO B7, SKIP TO B9.

NOTE: IF PARTICIPANT HAS A SUICIDE PLAN OR RESPONDS ‘YES’ TO ANY OF THE ITEMS FROM B7 ONWARD, END INTERVIEW AND REFER TO ALTERNATIVE RESOURCES.

B8 Intend to follow through on a suicide plan? NO YES 8

B9 Intend to die as a result of a suicidal act? NO YES 8

B10 Take any active steps to prepare to injure yourself or to prepare for a suicide attempt

in which you expected or intended to die? NO YES 9

How many times? _____

B11 Injure yourself on purpose without intending to kill yourself? NO YES 4

B12 Attempt suicide (to kill yourself)? NO YES 9

A suicide attempt means you did something where you could possibly be injured,

with at least a slight intent to die.

IF NO, SKIP TO B13:

How many times? _____

Hope to be rescued / survive π

Expected / intended to dieπ

**In your lifetime:**

B13 Did you ever make a suicide attempt (try to kill yourself)? NO YES 4

“A suicide attempt is any self-injurious behavior, with at least some intent (> 0) to die as a result or if intent can be inferred, e.g. if it is clearly not an accident or the individual thinks the act could be lethal, even though denying intent.”

(C-CASA definition). Posner K et al. Am J Psychiatry 164:7, July 2007.

| is at least **1** of the above (EXCEPT B1) coded **yes**?  If yes, add the total points for the answers (B1-B13)  checked ‘yes’ and specify the suicidality score as indicated in the diagnostic box:  make any additional comments about your assessment of this patient’s current  and near future suicidality in the space below:  If you do start having thoughts of suicide, or you begin to have a plan around suicide during this program, please make sure to let your therapist know. Since your therapist may not check their emails every day, it would be best if you phone them. You can also phone the Online Therapy Unit and speak to the co-ordinator for this project, [name]. If you are unable to reach your therapist or the co-ordinator, there is a suicide prevention tab on the website that lists other agencies you can call as well. If you feel as though you are at risk for committing suicide, you can also call 911 for help. | ***NO YES***  ***SUICIDALITY***  ***CURRENT***  1-8 points Low π  9-16 points Moderate π  > 17 points High π   |
| --- | --- |

**Participant must have LOW Current Suicide Risk to participate in program. If > Low, DISCUSS OTHER OPTIONS FOR TREATMENT; DOCUMENT DISCUSSION; CONSULT WITH SUPERVISOR IMMEDIATELY.

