***Method****.* Using a randomized controlled design, 58 women will be randomized to receive either TAICBT treatment or assigned to a 7-10 week WLC. Participants assigned to the WLC will receive a pamphlet that includes information on information on PPD and websites for support services offered in Saskatchewan. The intervention will consist of a seven-module TAICBT program adapted for women afflicted with PPD. Each TAICBT participant will be assigned to a therapist who they can correspond with weekly via email. Potential participants will be screened using the **Edinburgh Postnatal Depression Scale** (EPDS; Cox et al., 1987), modules from the **MINI International Neuropsychiatric Interview** (Sheehan et al., 1998), as well as standard screening questions. If deemed eligible, the following additional outcome measures will be administered: (a)**Depression Anxiety Stress Scale- Short Form** (DASS; Lovibond & Lovibond, 1995) to measure levels of depression, stress, and anxiety; (b)**Parenting Stress Index- Short Form** (PSI-SF; Abidin, 1995) to assess stress in the parent-child system; (c) **World Health Organization Quality of Life – BREF** (WHOQOL-BREF; WHOQOL Group, 1998) to assess quality of life;(d) **Therapist Alliance Questionnaire** (TAQ; Kiropoulos et al., 2008, modified from Luborsky’s 1985 HAQ-II) to determine the degree to which participants perceive the relationship with their therapist as helpful; (e) **Treatment Satisfaction Questionnaire-Modified** (TSQ; Cox et al., 1994) to assess the client’s perceived satisfaction with treatment; and (f) **Credibility/Expectancy Questionnaire**(CEQ; Devilly & Borkovec, 2000) to measure credibility and treatment expectancy of the TAICBT treatment. The TAQ, TSQ, and CEQ will only be completed by those participants receiving TAICBT treatment. All other measures will be completed by both groups of participants at pre-treatment and post-treatment (10 weeks after baseline). Following the 7-10 week wait, participants in the WLC group will be contacted, re-screened, and if still eligible, they will be offered the treatment. At this time, the TAICBT participants will be asked to respond to ten open-ended questions regarding their experiences with the program. To provide a longer-term follow-up of depressive symptoms, TAICBT participants will be contacted by telephone four weeks following treatment completion and administered the EPDS and the depression module of the MINI.

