All potential participants will participate in a telephone pre-screening and full-screening interview. When participants first contact the researcher, they will be informed of the nature of the study including the potential to be randomized to a waitlist condition (see Appendix X). The pre-screen interview will take approximately 15 minutes and will inquire about referral source, demographic questions, and questions about their symptoms (see Appendix B). To assess for severity of depressive symptoms, the Edinburgh Postnatal Depression Scale (Cox et al., 1987) will also be administered (see Appendix C). The full-screen interview will include additional demographic questions as well as the administration of the M.I.N.I. International Psychiatric Interview (M.I.N.I; Sheehan et al., 2006; see Appendices D and E). These interviews will be used to determine if they meet the inclusion and exclusion criteria established for the study.

As the current project is a randomized controlled trial, following the telephone screening and assessments, if the participant is eligible and interested in participating, she will be randomly assigned to either receive TAICBT treatment or to a 7-10 week waitlist group. Participants in both groups will be provided with a website link to a secure Canadian survey program (fluidsurveys.com). An information form and a consent form will be presented for the specific groups (see Appendices F and G). Each group will then be presented with a battery of baseline outcome measures (see Appendices H to M). These measures will take approximately 30 minutes to complete and will assess symptoms related to PPD, general stress, parental stress, quality of life, and treatment expectations.

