***TAICBT treatment***: Following completion of the baseline measures, the participants in the TAICBT condition will be provided with a login username and password to access Maternal Depression Online, which will be located at the following address: <http://www.onlinetherapyuser.ca>. As part of clinical practice, with client consent, a letter will be sent to the participant’s family physician informing them that their patient is participating in the Maternal Depression Online program (see Appendix N). This is done for two reasons. The first is to verify the client’s identity, and the second reason is to have a contact number in the unlikely case of an emergency. Upon initial login to the website, participants are provided with an information page and consent form (see Appendix G). The participants will then be offered the seven-module online treatment, with each module taking approximately one week to complete. Each module provides education about the disorder and assigns suggested exercises and homework to be completed in consort with an online therapist. The therapist communicates with their client once a week through emails that are contained within the Online Therapy USER website. Upon login for a new module, participants complete a weekly mood monitor (see Appendix O) and provide examples and answers questions from the previous module (see Introduction pages from http://www.onlinetherapyuser.ca/sitemap).

In order to assess change over time, following treatment completion, participants will be emailed the same website link to fluidsurvey.com to complete the post-treatment outcome measures along with measures related to therapeutic alliance (see Appendices H to M). The measures will take approximately 30-45 minutes to complete and will assess change in symptoms over the course of treatment. In addition to the measures, the participants will be asked to respond to a series of follow-up, open-ended questions regarding their experiences with the program (see Appendix P) as well as questions regarding any additional treatment they sought over the 10-week period (see Appendix O).

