***Pamphlet Condition***. In similar fashion to the TAU condition used in Austin and colleagues’ (2008) study, the participants who are randomly assigned to the TAU group will receive an information pamphlet that will be delivered via email (see Appendix Q). The MotherFirst campaign created an information pamphlet that is currently available to Saskatchewan healthcare providers, various support groups, and is displayed in places frequented by new mothers and their families. The chair of MotherFirst has agreed that the MotherFirst information pamphlet can be used for the purpose of the TAU condition. The pamphlet contains information on PPD symptoms and strategies to prevent and/or manage such symptoms. The pamphlet also includes a contact number and a website for postnatal support services offered in Saskatchewan (skmaternalmentalhealth.ca). Participants will be briefed over the telephone with the pamphlet information and informed of the postnatal support contacts should they choose to receive treatment. Seven to ten weeks following baseline measures, the participants will be emailed the same website link to fluidsurvey.com to complete the post-treatment outcome measures along with additional questions regarding any treatment they may have received during the wait time (see Appendix R). Following the completion of the post-treatment outcome measures, participants who received the pamphlet condition will be called over the telephone. They will be asked if they are still interested in receiving TAICBT. If they are screened eligible to participate according to the original screening criteria, the full treatment will be offered.

4. What information about the research project and their role will participants be given during the initial contact?

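### The suicidality advice in Appendix E, Module B is given before randomisation in one version that leads with 'your therapist', so this paragraph does not fit the 7-10 week wait (minor, wording only)

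*Protocol*

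**What the plan says.** **The advice.** The scoring box of Appendix E, Module B (Suicidality) contains a paragraph addressed to the participant. It concerns thoughts of suicide, or a plan, that start 'during this program', and its instruction is "please make sure to let your therapist know. Since your therapist may not check their emails every day". Because of the email delay, the paragraph prefers a phone call to the therapist. It then adds other routes: "You can also phone the Online Therapy Unit and speak to the co-ordinator for this project"; a suicide prevention tab on the website if neither therapist nor co-ordinator can be reached; and 911 for a woman who feels at risk. The entry rule stands under the same box: "Participant must have LOW Current Suicide Risk to participate in program".

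**When it is given.** Section III, item 3 places the MINI in the full-screen telephone interview. Only after the telephone screening, if eligible and interested, is a woman randomised: "she will be randomly assigned to either receive TAICBT treatment or to a 7-10 week waitlist group". Section III, item 4 confirms that she is told her arm after the telephone assessments.

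**Who has a therapist.** The Method summary says: "Each TAICBT participant will be assigned to a therapist who they can correspond with weekly via email". For the waitlist arm, Section III, item 3 (Pamphlet Condition) describes an emailed pamphlet and a telephone briefing: "Participants will be briefed over the telephone with the pamphlet information and informed of the postnatal support contacts should they choose to receive treatment". Treatment comes after the wait, subject to interest and a re-screen: "If they are screened eligible to participate according to the original screening criteria, the full treatment will be offered".

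**The concern.** The paragraph is safety advice for the participant and it looks forward: it covers thoughts that may begin after screening. It is delivered when nobody on the call knows the arm, so the screener cannot tailor it, and the module holds only one version. Its lead instruction nevertheless presupposes a therapist, whom only one arm has during the first 7-10 weeks.

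What is at stake is clarity in a crisis: a woman who recalls the main instruction while waiting would recall one that was not written for her situation. Error rates, sample size, estimation and analysis are not affected.

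**Working it through.** No arithmetic beyond counting applies. The check sets the relevant parts of the Protocol side by side.

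1. **Order of events** (Section III, items 3 and 4): pre-screen, then full-screen interview with the MINI (including Module B), then randomisation, then the woman is told her arm. The advice therefore precedes allocation.

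2. **Routes named in the paragraph** (Appendix E, Module B):

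| Route | How it is worded | Needs an assigned therapist? |
|---|---|---|
| Therapist, preferably by phone | Direct instruction | Yes |
| Online Therapy Unit co-ordinator by phone | Offered as an option | No |
| Suicide prevention tab on the website | Fallback if the first two cannot be reached | No |
| 911 | Option for a woman who feels at risk | No |

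   Count: 4 routes, of which 1 needs a therapist, leaving 4 − 1 = 3 that do not. The one that needs a therapist is also the only one phrased as a direct instruction. The phrase 'your therapist' occurs 3 times in the paragraph.

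3. **Who can use the first route during the wait.** Therapist assignment is described for TAICBT participants (Method). For waitlisted women, treatment is offered only after the 7-10 weeks and a re-screen (Section III, item 3).

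4. **What 'program' means.** Two readings are possible:
   - *The treatment.* Section III, item 3 says "participants in the TAICBT condition will be provided with a login username and password to access Maternal Depression Online", and Section III, item 4 describes that program by its modules and the online therapist's part in it. On this reading the paragraph is correct for women in treatment but does not address the wait.
   - *The study.* The entry rule quoted above uses 'program' and is applied to every woman screened, before allocation. On this reading the paragraph covers the wait but directs a waitlisted woman to a therapist she does not yet have.

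   The wording falls short on either reading, so the point does not depend on which is right. The first is the more natural.

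5. **Does the entry rule make the advice redundant?** No. The rule concerns current risk at screening, whereas the advice concerns thoughts that start later.

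6. **Number of women affected.** Not computed. The Protocol plans 58 women in total. The text under review gives no allocation ratio and no rate of new suicidal thoughts, so no exposure or harm figure can be supported.

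**The case against.** The strongest defence is that the instruction carries its own condition. Across the Protocol, 'program' mostly means the online treatment. The pre-screen interview (Appendix B) separates the program's format from the research. The full-screen interview (Appendix D) and the physician letter (Appendix N) attach the word to the Online Therapy USER service. The entry rule does not redefine it, because screening determines who is suitable for that service. Read this way, the sentence applies when a woman is in treatment and has a therapist, and it gives a waitlisted woman no instruction that she cannot carry out. Women who reach treatment after the wait are screened again on the original criteria, which include suicide risk.

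Much of this stands. A reader might infer that the lead step *cannot be followed in one arm*. That is too strong: on the natural reading, the step is not addressed to a woman who is waiting. What remains is that the paragraph is then silent about the wait, and a woman hearing it before allocation is not told which contact applies if she is waitlisted. The re-screen does not fill that interval, since it comes at its end.

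The second line of defence is that the wait is covered elsewhere. The co-ordinator's line, the website tab and 911 do not depend on having a therapist. The Pamphlet Condition includes a telephone briefing on support contacts. Appendix W calls for supervisor involvement even when a screened woman's risk is low. The waitlist information and consent form (Appendix F) and the opening telephone script (Appendix X) are not in the text under review and may say more. This also stands, and it limits the point to one paragraph.

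**Conclusion.** The point holds as a minor wording defect in one participant-facing paragraph. Its lead instruction is written for women in treatment, it is given before anyone knows who will be treated, and on neither reading of 'program' does it properly serve a woman during the 7-10 week wait. In size, 1 of 4 named routes depends on an assigned therapist, and that route comes first and is the only direct instruction. There is no statistical consequence. I class it as a cheap improvement for patient safety.

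A reader might go further and infer that waitlisted women are left without a crisis route, or that the plan as a whole does not cover the wait. The documents do not support either inference. Three routes in the same paragraph need no therapist, support contacts are given after allocation, and the waitlist consent form cannot be judged here.

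The conclusion rests on two assumptions: that the paragraph is read to the participant, which is inferred from its second-person wording, and that no therapist is assigned during the wait, which follows from the Method and the Pamphlet Condition as described.

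**What to change.** Reword the paragraph in Appendix E, Module B so that it works in both arms:

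- name the Online Therapy Unit co-ordinator by phone first, with 911 for immediate risk;
- then name the therapist, with the words 'once you have been assigned one';
- keep the website tab as a further source;
- replace 'during this program' with 'at any time during the study, including while waiting'.

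The cost is one script revision and a notice to the research ethics board. No staff, contacts or data are added, and the design and analysis are unchanged.
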